## Background

Idiopathic nephrotic syndrome (INS) is a rare disease that predominantly affects young children. In the Netherlands, the yearly incidence is 1.52 per 100 000 children (an estimated 60 new cases per year).^1^ INS is characterised by proteinuria, hypoalbuminaemia and oedema. It is often accompanied by hyperlipidaemia. Initial treatment consists of 8–20 weeks of corticosteroids, of which at least 4 weeks single-daily dose of 60 mg/m^2^ followed by an alternate schedule.^2^ The vast majority of patients shows remission within 4 weeks, after which the diagnosis minimal change disease is assumed and no kidney biopsy is indicated.^3^ Unfortunately, 80% of the responders experience at least one relapse; half of those patients experiencing frequent relapses (FRNS) or becoming steroid-dependent (SDNS).^4^ Relapses are further treated with steroids; however, steroids are associated with many side effects.^5^ In these cases, steroid-sparing drugs are recommended.^2^ These include cyclophosphamide, calcineurin inhibitors, mycophenolate mofetil (MMF) and rituximab. But still, all come with substantial toxicity. A promising steroid-sparing agent is levamisole, an anthelminthic drug mostly used in a veterinary setting. Levamisole is, contrary to other steroid-sparing drugs, not an immunosuppressant, but acts as an immunomodulator. It has relatively few side effects of which neutropenia is the most serious and most common that requires frequent check-ups. Recent trials show a beneficial effect of adjuvant treatment with levamisole to corticosteroids in children with FRNS or SDNS, but also that treatment is safe.^6–8^

In order to prevent the frequency of relapses, several steroid schedules for the treatment of the first episode of INS have been studied, for instance, comparing a longer with a shorter course.^4^ To our knowledge, no trials have been performed investigating the efficacy of levamisole as an adjuvant agent to initial steroid treatment on preventing relapses. Currently, a study similar to ours is underway in France (Nephrovir-3).

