### Objectives

The primary objective of the study is to investigate the effect of additional levamisole to standard steroid therapy in comparison with placebo from 4 to 28 weeks (figure 1) after the start of the first episode of steroid-sensitive INS (SSNS) in children (age 2–16 years) on the occurrence of any relapse within 12 months after first presentation.

Secondary objectives are:To investigate differences between the two study groups in time to first relapse, the number of relapses, cumulative steroid dosage and the occurrence of SDNS and FRNS in a 2-year period.To investigate HRQoL, psychosocial adjustment, parental distress at different stages of treatment (longitudinal and cross-sectional) and to identify medical and personal factors related to HRQoL.To investigate the consequences of the disease on days of missing school for children, (financial) problems for parents, outpatient visits and hospital admissions.

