### Study endpoints

The primary endpoint of the study is the occurrence of a first relapse within 12 months (week 52) after first presentation. Relapse is defined as having proteinuria (3+ on urine dipstick confirmed by >200 mg/mmol creatinine on quantitative urinalysis) for three consecutive days.

Secondary endpoints can be found in box 2.Box 2Secondary endpoints are being compared between the intervention groupsTime to first relapse (days).Relapse rate over 2-year period (n/year).Cumulative steroid dose over 2-year period (mg/m^2^).Number of (serious) adverse events (n).Number of treatment discontinuations (n).Proportion patients with FRNS or SDNS (%).Days of missing school (days), outpatient visits (n), hospitalisation days (days).HRQoL and psychosocial adaptation at different time points (see table 1):Cross-sectional and longitudinal.Comparison with healthy peers and other chronic diseases.FRNS, frequent relapsing nephrotic syndrome; HRQoL, health-related quality of life; SDNS, steroid-dependent nephrotic syndrome.

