### Sample size

Sample size was calculated based on the superiority design of the trial, as well as on the intention-to-treat principle and on the primary outcome of the study: occurrence of relapse within 12 months after first presentation. To achieve a power of 80% with a two-sided significance level of 5%, two groups of 41 subjects are needed to identify a reduction in relapse of 30% (from 75% relapse to 45%), which is considered clinically relevant. A total of 82 patients need to complete 2 years of follow-up. With an estimated drop-out rate of 10%, 92 patients in total need to be included for the RCT. It is expected that around 90% of all children with a first episode of INS will be steroid sensitive.^22 23^ Additionally, we expect that about 65% of the patients screened for eligibility are willing to participate.^4^ In conclusion, this means a total of 157 patients need to be recruited. With an incidence of 60 new cases of INS per year in the Netherlands and 30 new cases per year in Belgium (estimated), an inclusion period of 2 years is expected. After withdrawal of informed consent, no study subjects will be replaced.

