### Randomisation

A total of 92 eligible patients will be randomly assigned to one of the two treatment arms in a 1:1 ratio, receiving either levamisole (treatment) or placebo (control) added to standard corticosteroid treatment. Block randomisation will occur using block sizes of 2, 4 and 6, which will be randomly used in order to make concealment of allocation as accurate as possible while granting minimal differences in numbers between the two groups. Randomisation (week 4) will be performed by the local investigator using CastorEDC. The local investigator is blinded for the outcome of randomisation; only members of the AMC clinical pharmacy have rights to view allocation of treatment. Patients, parents, medical and nursing staff, outcome assessors, monitors and data analysts are blinded to treatment allocation.

Treatment allocation will be blinded until the study has ended, all data has been collected, queries have been resolved and the database has been locked.

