### Statistical analysis

The outcomes of all included study subjects will be analysed as intention-to-treat. For safety analysis, an ‘as treated’ population will be defined. Study subjects who are lost to follow-up, withdraw informed consent or stopped study medication prematurely will be analysed according to allocated treatment group (figure 2). All data that have been collected until withdrawal or lost to follow-up will be used for analyses. Missing values at baseline and/or follow-up will not be imputed. R Studio will be used for performing all statistical analyses. A p value of <0.05 will be considered statistically significant. Continuous data will be presented as means with SD or median with IQR, depending on distribution. For between group comparisons, a Student’s t-test in case of normal distribution or Mann-Whitney U test in case of non-normal distribution will be used. Categorical data will be presented as proportions and compared using a χ^2^ test. The primary outcome, the occurrence of a relapse at 1 year after first presentation, will be compared between groups using a χ^2^ test. Relapse-free survival will be presented as a Kaplan-Meier survival curve. Multivariate analyses (age at onset, sex, ethnicity, time to remission and FRNS/SDNS) will be performed using Cox regression.

No interim analysis for either efficacy or futility will be performed. Safety reviews will be performed by the Data Safety Monitoring Board (DSMB) after 1 year or when 25 patients have been included and have completed the 24 weeks (week 28 after first presentation) using study medication.

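### FRNS/SDNS can arise only after randomisation and is itself an endpoint, yet it is listed as a term in the secondary Cox regression; if that model estimates the treatment effect on first relapse, the adjusted hazard ratio is not interpretable

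*Protocol article*

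**What the plan says.** The Statistical analysis section of the protocol article gives the primary outcome, relapse by one year, a chi-squared test. It then turns to time to event: "Relapse-free survival will be presented as a Kaplan-Meier survival curve". The next sentence reads: "Multivariate analyses (age at onset, sex, ethnicity, time to remission and FRNS/SDNS) will be performed using Cox regression". It does not name the outcome of the Cox model, and it does not say that treatment arm is a term.

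FRNS/SDNS appears elsewhere in the article as a result of the disease course:

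- Background: about half of the children who relapse go on to frequent relapses or steroid dependence.
- Objectives: a secondary objective is to compare the arms on "the occurrence of SDNS and FRNS in a 2-year period".
- Study endpoints, Box 2: the secondary endpoints compared between the arms include "Proportion patients with FRNS or SDNS", alongside time to first relapse.

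On timing, Box 1 excludes any child with an earlier episode and requires remission within four weeks of steroid treatment. The Randomisation section adds: "Randomisation (week 4) will be performed by the local investigator using CastorEDC".

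**The concern.** A covariate in a model for a randomised treatment effect should be known at randomisation or be unaffected by treatment. Age at onset, sex, ethnicity and time to remission meet that test. FRNS/SDNS does not. No child carries the label at week 4, and a child can acquire it only by relapsing, which is what levamisole is meant to prevent. A child who never relapses can never carry it.

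At stake is the adjusted hazard ratio for first relapse. Time to first relapse is the first endpoint in Box 2, and Cox regression is the only between-arm method named in the article that handles censoring. Its estimate is therefore likely to be reported next to the Kaplan-Meier curve. If levamisole lowers both the risk of a first relapse and the chance of FRNS/SDNS, the model attributes part of the benefit to the covariate.

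**Working it through.** **1. Can FRNS/SDNS be a baseline variable?** Earlier episodes are excluded (Box 1), randomisation is at week 4 in remission (Randomisation), and FRNS/SDNS develops among children who relapse (Background) and is counted over two years (Objectives). Its value at randomisation is therefore zero for every child.

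**2. Does any coding of the term work in a model for first relapse?**

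- As a fixed indicator (ever FRNS/SDNS), it uses information from after the event. Every labelled child has relapsed.
- As a time-dependent covariate, it is zero for as long as a child is at risk of a first relapse, so it contributes nothing.
- As a separate outcome, it does not belong in a list with four predictors.

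To illustrate, apply the Background share (half of relapsers) to the planned 12-month rates. The label would fall on 0.75 × 0.5 = 37.5% of controls and 0.45 × 0.5 = 22.5% of the levamisole arm. That difference is part of the treatment effect, and the model would hold it fixed.

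**3. The plan's own figures.** The Sample size section states: "To achieve a power of 80% with a two-sided significance level of 5%, two groups of 41 subjects are needed", for a fall "from 75% relapse to 45" per cent. With mean proportion 0.60:

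n = [1.96 √(2 × 0.60 × 0.40) + 0.8416 √(0.75 × 0.25 + 0.45 × 0.55)]² / 0.30² = (1.358 + 0.555)² / 0.09 = 40.7, so 41 per arm (power 80.3%).

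With 10% dropout, 82 / 0.90 = 91.1, so 92. Both figures reproduce, and neither involves the Cox model.

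**4. Reference hazard ratio.** Under constant hazards, 75% v 45% at 12 months implies ln(0.55) / ln(0.25) = 0.598 / 1.386 = 0.431.

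**5. Size of the distortion (simulation, 82 children, 600 runs per row).** Relapses follow a Poisson process over two years with gamma frailty, calibrated to 75% v 45% at 12 months. The treatment effect persists on later relapses. Cox models for first relapse contain treatment alone, or treatment plus an ever-FRNS/SDNS indicator. The labelling rules are assumptions.

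| Assumed FRNS/SDNS rule | Frailty variance | Labelled | HR without | HR with | p<0.05 without | p<0.05 with |
|---|---|---|---|---|---|---|
| ≥2 relapses in first 6 months or ≥4 in any 12 | 0 | 15% | 0.42 | 0.50 | 91.2% | 72.0% |
| same | 0.5 | 26% | 0.44 | 0.63 | 86.7% | 36.2% |
| same | 1 | 33% | 0.44 | 0.70 | 88.0% | 24.5% |
| ≥3 relapses in 2 years | 0 | 32% | 0.43 | 0.62 | 93.3% | 38.3% |
| same | 0.5 | 39% | 0.44 | 0.70 | 89.3% | 24.0% |
| same | 1 | 43% | 0.44 | 0.71 | 88.2% | 20.2% |
| random half of relapsers | 0 | 41% | 0.43 | 0.47 | 92.3% | 85.0% |
| same | 0.5 | 39% | 0.44 | 0.49 | 90.5% | 81.8% |
| same | 1 | 37% | 0.44 | 0.48 | 87.8% | 78.5% |

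Monte Carlo error on a percentage is at most √(0.25 / 600) = 2 points. A few adjusted fits did not converge in two rows (576 and 596 of 600 were usable). With no treatment effect (first rule, frailty 0.5), the adjusted hazard ratio was 1.00 and 3.7% of runs rejected, against 5.3% unadjusted.

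**6. A second set of simulations**, with 46 per arm, exponential gaps between relapses and gamma frailty in the main version, plus simpler versions:

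- Effect persisting on later relapses: HR 0.39-0.41 to 0.63-0.67, power 87-94% to 26-31%.
- Half of relapsers labelled, mainly through early relapse: HR 0.43 to 0.51, power 88% to 66%.
- Label random among relapsers: for example HR 0.43 to 0.45.
- Effect ending at first relapse: for example HR 0.41 to 0.39.

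**The case against.** **The primary result does not depend on this model.** This stands. Relapse at one year has its own unadjusted chi-squared test, and the sample size rests on that outcome alone. The Kaplan-Meier curve is unadjusted, and FRNS/SDNS keeps its own comparison between arms. A reader might infer that the trial's main conclusion is in danger; the article does not support that.

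**The model is partly inferred.** This also stands. The sentence names neither the outcome nor a treatment term. First relapse follows from the preceding sentence and from Box 2. A prognostic-factor model, or a loose list that mixes predictors with an outcome, is possible. In a prognostic model the bias in the treatment effect would not follow, but explaining first relapse by a label that requires relapse would be circular. A fuller protocol or analysis plan may settle the outcome and the treatment term, but it would not make the printed list correct.

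**The size rests on assumptions.** This stands too. The article gives no numerical definition, and the large shifts need an assumed rule and an effect that persists after the first relapse. With a random half of relapsers the shift is modest, and in one scenario it runs slightly away from 1. A reader might infer that the adjusted analysis is bound to turn a clear benefit into a null result; the range does not support that.

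**No false-positive risk was shown.** Correct for the one null scenario that was run. What was found is mainly attenuation of a real effect.

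**Conclusion.** The covariate list is wrong as written. FRNS/SDNS cannot be a valid adjustment term for time to first relapse under any coding, because it is unknown at randomisation, requires the event, and is an endpoint that treatment may change. If the model includes treatment and concerns first relapse, as the context implies, its adjusted hazard ratio does not estimate the treatment effect.

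The fault is confined to a secondary analysis. It should be fixed, but it does not threaten the primary test, its power or the total of 92. That FRNS/SDNS is an invalid covariate follows from the article alone; the size of the distortion does not. Across both sets of simulations the hazard ratio moved from about 0.39-0.45 to about 0.39-0.71, mostly towards 1. The share of significant results fell by as little as 7 points (92.3% to 85.0%) or as much as 68 (88.2% to 20.2%) in the table above. These figures assume particular FRNS/SDNS rules, frailty variances and degrees of persistence of the effect, and should be read as a range and not as a prediction.

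**What to change.** In the Statistical analysis section, or in the analysis plan if that governs:

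- Delete FRNS/SDNS from the Cox covariates.
- State that the outcome is time to first relapse and that the model contains treatment arm plus age at onset, sex, ethnicity and time to remission.
- Keep FRNS/SDNS only as a secondary outcome compared between the arms.
- If the sentence was meant to announce a separate analysis of FRNS/SDNS, say so in a sentence of its own.

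The cost is one or two sentences. Data collection, design and sample size do not change. Allocation stays blinded until database lock, so the change should be made and dated before unblinding; it then cannot look driven by results.

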### Monitoring and safety

A risk analysis according to guidelines of the Dutch Federations of University Hospitals categorises the study as ‘moderate risk’. Although the risk of the study is considered negligible, our paediatric study population may be considered vulnerable and, therefore, the risk was upgraded to moderate. The Clinical Research Unit of the AMC will monitor the study, both on site and remotely.

Additionally, a DSMB is established to oversee the inclusion rate and to protect the safety of the study subjects and the integrity of the study data. The DSMB consists of four members: a paediatrician with experience as a member of the ethical committee (chair), a paediatric nephrologist, two methodologists and a nephrologist, all independent of the trial. The DSMB will meet every 6 months, or sooner in case of a suspected unexpected serious adverse reaction (SUSAR). After 1 year or after 25 subjects (whichever occurs first) have been included and completed 24 weeks of treatment with study medication, a safety assessment will be performed. No stopping rules have been defined. The coordinating study team is responsible for reporting serious adverse events and submitting annual safety reports to the central Medical Ethical Committee (MEC) and competent authority. SUSARs will be reported to the competent authority and MEC by ACE Pharmaceuticals in order to keep the study team blinded. The AMC clinical pharmacy will provide unblinding on request after approval by the principal investigator.

### Patient and public involvement

The Dutch Kidney Patient Association (NVN) was involved in the design of the study. Together with the patients, the burden of the intervention was discussed, and, on special request from the NVN, a HRQoL study was implemented in the design. All published data will be made available to the patients through email and the study’s website.

## Ethics and dissemination

### Ethical approval

A notification of no objection has been obtained from the Dutch and Belgian competent authorities: Central Committee on Research Involving Human Subjects (CCMO) and Federal Association of Health and Medicinal Product, respectively. Substantial amendments will be submitted for review to the MECs and competent authorities. The study is registered at the EU Clinical Trials Register under number NL61906.018.17. The study will be conducted in line with the Declaration of Helsinki (2013) and the International Conference of Harmonisation-Good Clinical Practice guidelines.

### Informed consent

Before any study-related (screening) procedures occur, written informed consent must have been obtained from patient’s parents or legal representatives and/or the patient, depending on the patient’s age. Children aged 12 years and older need to sign informed consent in addition to their parents. Children <12 years of age will be informed about the study in a manner that matches their age and understanding. Patients and their parents will be informed about their right to withdraw consent at any time without having to provide reasons. In case of resistance of the patient to any of the study procedures, the ‘*Code of conduct involving minor’* will be used as a guideline. PIFs and informed consent forms are all approved by the MEC.

### Confidentiality

All patients have their own patient ID, generated by the hospital information system. Source data will be stored confidentially at the local sites under this patient’s hospital ID. Study data will be kept using a unique patient identification number. The investigators will keep this number strictly confidential. Only the investigators have access to the key. Handling personal data will comply with the latest General Data Protection Regulation Act (EU Directive, 25 May 2018). All data will be stored for 15 years after the end of the study.

### Dissemination policy

Prior to the start of the study, the LEARNS study was registered in the Dutch Trial Registry. Results will be published in (inter)national peer-reviewed scientific journals once the study is completed. Papers will be published according to the CCMO and International Committee for Medical Journal Editors guidelines. Final results will be made public to all participants.

## Discussion

The LEARNS study aims to demonstrate the efficacy and safety of adding levamisole to standard steroid therapy in children with a first episode of INS on reducing relapses by conducting a multicentre randomised, double-blind, placebo-controlled trial.

Previous research mainly focused on the duration and cumulative doses of prednisolone in children with a first episode of INS. Initially, longer duration of prednisolone treatment was considered superior in order to prevent relapses. Recent, well-conducted studies have shown that treating patients with prednisolone longer (2 or 3 vs 6 months) has no beneficial effects on relapse-free survival.^4 24–26^ Still, in both groups, around 80% of the children experience one or more relapses. In 2006, a study by Hoyer *et al* on the efficacy of cyclosporine as adjuvant to steroid therapy for a first episode of INS showed a significant decrease in relapses in the first 12 months. However, this effect disappeared after 18 months. Because of the high rate of adverse effects and the need for blood monitoring, the authors did not recommend the protocol as standard therapy for these patients.^27^ Currently, the INTENT (Initial treatment of steroid-sensitive idiopathic nephrotic syndrom in children with mycophenolate mofetil versus prednisone) study is ongoing. This open-label, randomised trial compares prednisone versus MMF as initial treatment in children with a first episode of SSNS.^28^ However, apart from these few studies, no further improvement in the prevention of relapses after the first episode of INS has been made.

Relapses of INS consequently result in repeated courses of prednisolone and are often accompanied by steroid toxicity. Therefore, INS comes with a high burden of disease affecting HRQoL of both patients and their families. Although it is known that HRQoL is impaired in children with kidney disease, these studies were mainly performed in children with end-stage renal disease.^29^ Only few studies have been published on HRQoL in children with INS.^30–33^ Not only do these children report a lower HRQoL compared with healthy peers, their parents report an even more pessimistic view.^31^ Additionally, it appears that the duration of the disease has a negative impact on HRQoL.^32^ However, these studies are of cross-sectional design and did not include disease status or medication. Preventing relapses may thus contribute to improving quality of life in INS patients and their families.

Levamisole is a promising steroid-sparing agent since it has relatively few side effects compared with other steroid-sparing drugs. This has been shown in several RCTs in children with FRNS and SDNS.^6–8 12 34–37^ Its mode of action is still poorly understood. It is believed that levamisole has immunomodulatory effects by shifting the Th2 immune response to a Th1 response,^9 10^ and/or has a direct effect on the podocyte by inducing glucocorticoid receptor signalling pathway and, in this way, mimics or enhances the effect of prednisolone.^38^

Furthermore, it must be stressed that in preventing the progression of INS to a chronic illness, research should focus on a permanent cure of the disease. We hypothesise that adding levamisole to the standard treatment with corticosteroids in children with a first episode of INS will prevent future relapses and, thus, will contribute to a better quality of life by reducing the cumulative steroid dose.

Since a similar trial on the efficacy of levamisole is simultaneously conducted in the Paris area, we adapted the French protocol for initial steroid treatment of INS. The study treatment and primary outcome is similar in both studies, but the duration of follow-up is different: 12 months compared with 24 months in our study. Additionally, HRQoL questionnaires were originally not implemented, but Nephrovir-3 has planned to participate in our HRQoL study.

The main strength of our study is its randomised, placebo-controlled design, conducted in 20 participating hospitals in the Netherlands and Belgium. In this way, an extensive, geographical area will be covered. Placebo-controlled RCTs remain the golden standard in comparing different treatment regimens. On the other hand, an important limitation of this study may be the size of the study population. We only powered for our primary outcome, not for subgroup analyses. In case of insufficient inclusions, we may pool our data with the Nephrovir-3 trial since we use similar treatment protocols. Another limitation may be that the treatment of relapses is not standardised by our study protocol as we mainly focus on the initial treatment. However, in the Netherlands, relapses are almost always treated according to national guidelines.^39^

After completion, the LEARNS study may provide evidence for adjusting (inter)national protocols for the standard treatment of the first episode of INS. If adding levamisole would prevent relapses, the disease could be less prevalent and the burden of disease on both patient and society be lowered. This could also mean that repeated courses of corticosteroids will be no longer needed and toxicity will be minimal. Additionally, and not the least important, quality of life of the patients and their families could be improved.

